## Abstract

**Background:** Dental treatment often requires prolonged mouth opening. This may compromise comfort during spontaneous nasal breathing and saliva swallowing, leading to stress or anxiety. A high-flow nasal cannula (HFNC) delivers warmed and humidified air at high flow rates and may improve breathing comfort; however, the feasibility of its routine use during dental treatment has not been established. **Objectives:** The primary objective of this pilot study is to evaluate the feasibility of conducting a definitive clinical trial to investigate the use of a HFNC during dental treatment. The secondary objective is to explore preliminary patient-centered outcomes related to stress and comfort to inform the design of future clinical trials. **Methods:** This single-center, open-label pilot feasibility study will be conducted at Nagasaki University Hospital, with adult patients undergoing routine full-mouth periodontal treatment participating in two treatment sessions, one without a HFNC and one with a HFNC, separated by at least four weeks. The primary feasibility outcomes include recruitment and retention rates, patient tolerance and acceptability of the HFNC, completeness of data collection, and device-related adverse events. The secondary outcomes are exploratory and include physiological stress-related parameters (pulse rate, respiratory rate, autonomic nervous system indices, and electroencephalographic alpha wave activity) and patient-reported comfort assessed using a questionnaire. **Conclusions:** This pilot study was designed to assess the feasibility and safety of HFNC use during full-mouth periodontal treatment and to inform the design of future definitive clinical trials. In particular, the resultant exploratory patient-centered outcomes and preliminary data may be used to guide outcome selection and sample size estimation.

## 1. Introduction

Dental treatment frequently requires patients to maintain a wide-open mouth for prolonged periods while breathing through the nose. This posture can make nasal breathing and swallowing difficult, resulting in discomfort, anxiety, and stress. In some patients, maladaptive breathing patterns, such as hyperventilation or breath-holding, may occur as coping strategies, potentially compromising both patient comfort and procedural safety. Dental anxiety and treatment-related distress remain common clinical problems. Contemporary evidence highlights persistent gaps and heterogeneity in interventions aimed at reducing acute anxiety during dental procedures, underscoring the need for pragmatic, low-burden approaches that can be integrated into routine workflows [1].

High-flow nasal cannula (HFNC) therapy delivers warm and humidified air or oxygen at high flow rates. HFNCs are widely used in medicine, anesthesiology, and critical care. The HFNC is known to generate low levels of positive airway pressure, wash out nasopharyngeal dead space, and reduce breathing during spontaneous respiration [2]. Previous experimental and clinical studies have suggested that the HFNC may facilitate the swallowing of saliva and improve the coordination between breathing and swallowing under spontaneous breathing conditions [3,4,5,6,7]. These physiological effects indicate that the HFNC may be a biologically plausible intervention for improving breathing comfort during dental treatments. Available in vitro and volunteer physiological data indicate that the HFNC can generate measurable airway pressure effects and modulate breathing patterns. The magnitude of these effects is influenced by mouth opening/closure, an issue directly relevant to dental treatment where sustained mouth opening is often unavoidable [8]. Physiological studies in patients with spontaneous breathing further support the concept that the HFNC can improve breathing efficiency, consistent with the upper-airway dead-space washout mechanism [9].

Despite their increasing use in other clinical settings, the feasibility of using HFNCs during routine dental treatments has not been adequately investigated, and patient tolerance of HFNCs during dental procedures and the practicality of using HFNCs in dental clinics are yet to be determined. Likewise, the feasibility of collecting physiological and patient-reported outcome data in this setting is uncertain. Although a recent scoping review summarized the application of HFNCs during dental procedures with sedation, the evidence base remains limited. Available evidence is primarily related to oxygenation/ventilatory endpoints under sedation. Importantly, the feasibility of HFNC use in routine (non-sedated) dental treatment has not been sufficiently investigated [10].

Feasibility-related uncertainties must be addressed before conducting a fully powered effectiveness trial. The primary objective of this pilot study is to assess the feasibility of a definitive clinical trial to evaluate the use of a HFNC during dental treatment. The secondary objectives are to explore preliminary patient-centered outcomes related to stress and comfort to inform outcome selection, study procedures, and sample size estimation for a future clinical trial.

## 2. Methods

### 2.1. Study Design

This is an investigator-initiated, single-center, open-label pilot feasibility study that will be conducted at Nagasaki University Hospital, Japan. The study was designed in accordance with the Consolidated Standards of CONSORT extension for pilot and feasibility trials and the principles of the Declaration of Helsinki. Ethical approval was obtained from the Clinical Research Review Board of Nagasaki University, and the study is registered with the Japan Registry of Clinical Trials (jRCTs072240099). Given the exploratory nature of the research question and the need to evaluate feasibility-related parameters before a definitive trial, a pre–post, fixed-sequence, within-subject feasibility design was adopted.

As illustrated in Figure 1, this pilot study was specifically designed as a feasibility-oriented, pre–post, fixed-sequence, within-subject study to evaluate the practicality, acceptability, and safety of high-flow nasal cannula (HFNC) use during routine full-mouth periodontal treatment, rather than to assess clinical effectiveness. Participants will undergo two dental treatment sessions, one without a HFNC and one with a HFNC, separated by a washout period of at least four weeks.

The research design, measurement items, and evaluation indicators for high-flow nasal cannula (HFNC) intervention in full-mouth periodontal treatment are shown in Figure 1, which illustrates the structured approach to evaluating the impact of a HFNC during full-mouth periodontal treatment in a fixed-sequence, pre–post, within-subject feasibility design.

Research design (Pre–Post, Fixed-Sequence, Within-Subject Feasibility Design): The study will be conducted in two sessions separated by a washout period of 4 weeks.

Session 1 (Baseline Data Collection): Dental treatment will be performed under standard conditions without a HFNC to establish baseline physiological and psychological data.

Session 2 (HFNC Intervention): Dental treatment will be performed while delivering 20–30 L/min of heated and humidified air via a HFNC to measure the intervention’s impact.

Measurement items: Data collected include physiological indicators such as Pulse Rate (PR), Heart Rate Variability (HRV: LF/HF), Respiratory Rate (RR), and Brain Waves (EEG alpha), as well as patient-centered metrics like Quality of Life (QOL) and Satisfaction.

The primary outcomes are feasibility parameters, including recruitment and retention rates, patient acceptability and tolerance of the HFNC, completeness of physiological and questionnaire-based data collection, and device-related adverse events. The secondary outcomes are exploratory and include physiological and patient-centered measures to inform outcome selection and sample size estimation for a future definitive clinical trial.

This design allows each participant to serve as their own control and enables comprehensive assessment of feasibility outcomes, including patient tolerance, data completeness, and device-related safety, under real-world dental treatment conditions.

### 2.2. Participants

Adult patients (aged ≥ 18 years) undergoing routine full-mouth periodontal treatment at the Department of Special Care Dentistry, Nagasaki University Hospital, will be eligible for inclusion. Written informed consent will be obtained from all participants prior to enrolment.

### 2.3. Inclusion Criteria

Patients visiting the Nagasaki University Hospital Dental Department for regular management and scheduled to undergo full-mouth periodontal disease treatment (periodontal pocket cleaning);Age ≥ 18 years at the time of consent;Ability to understand the study procedures and complete questionnaires independently.

### 2.4. Exclusion Criteria

Inability to breathe through the nose;Cognitive impairment precluding questionnaire completion;Pregnancy;Any condition deemed unsuitable by the principal investigator.

### 2.5. Study Procedures

After providing informed consent, participants will undergo full-mouth periodontal treatment (approximately less than 30 min in the supine position without a rubber dam under High-Capacity Dental Suction conditions) in two different sessions. During the first session, full-mouth periodontal treatment will be performed without the use of a nasal cannula or other respiratory devices. Participants will subsequently complete a self-administered questionnaire. In the pre–post, fixed-sequence, within-subject feasibility design, stress during the second session may decrease independently of the HFNC due to factors such as habituation, reduced treatment volume/invasiveness, and changes in psychological adaptation. Therefore, the following points will be carefully considered. The two sessions will be conducted and standardized at the same time of day, by the same operator with five years of clinical experience using same instrumentation type with consistent treatment extent and duration, and each session involves the treatment of only one side of the jaw or one quadrant within the full-mouth periodontal treatment area in a total of two sessions. In addition, to minimize the possibility of marked changes in periodontal status by the second session, the interval between the two sessions will be limited to within four weeks.

The second full-mouth periodontal treatment session will be scheduled for at least four weeks after the first session. During this session, full-mouth periodontal treatment will be performed with a dedicated HFNC (AIRVO3, Fisher & Paykel Healthcare Ltd., Auckland, New Zealand). Prior to the start of treatment, the nasal cannula will be inserted into both nostrils, and warmed and humidified air will be delivered at an initial flow rate of 20 L/min. If no discomfort is reported, the flow rate will be gradually increased to a maximum of 30 L/min. The AIRVO3 HFNC will be applied with fixed FiO_2_ at 0.21 at a temperature of 37 °C, with appropriate matched cannula size (S, M, L size) for all patients and criteria for flow escalation and discontinuation.

During both sessions, physiological parameters will be continuously monitored, including pulse rate, respiratory rate, and electrocardiographic RR intervals. Autonomic nervous system activity will be assessed using heart rate variability analysis (LF/HF ratio) using an MWM20 ECG monitor (GMSCo., Ltd., Tokyo, Japan) (sampling rate 200 Hz, 30 s window, placing ECG electrode on the anterior chest and behind the ears). For the ECG analysis, RR intervals will be resampled at 1000 Hz. The pulse rate and respiratory rate will be summarized as mean intra-procedural values and the value of LF/HF will be calculated over a fixed 2 min segment. The baseline measurement is defined as a value before the start of high-flow therapy, percent changes against baseline value will be derived for change score, and the missing or low-quality signal segments will be carefully checked with existence of large artifact or noise signals.

Stress-related electroencephalographic activity will be evaluated by assessing alpha wave appearance rates using the MWM20 EEG monitor (sampling rate 200 Hz, 2 s window, placing EEG electrode on the forehead and behind the ears). Following treatment, participants will complete a questionnaire assessing comfort and anxiety. Because electroencephalography (EEG) signals are susceptible to artifacts, particularly from electromyographic activity caused by blinking and eye movements, preparatory measures will be taken to minimize artifact contamination. During measurement, participants will be required to keep their eyes closed and remain in an environment designed to prevent body movement, and recordings will be performed in an environment designed to prevent body movement. During electrocardiography (ECG), RR intervals will be analyzed; therefore, automatic processing for arrhythmia detection and noise removal will be applied. A zero-phase filter and a hum filter will be used as baseline settings. EEG recordings will be obtained using a monopolar derivation with a reference electrode placed behind the ear.

No waveform correction will be performed during measurements using either the MWM20 EEG or ECG monitor. In the dental treatment setting, swallowing, mandibular movements, instrument noise, and body motion may also further interfere with EEG α-wave recordings. Therefore, the protocol restricts measurements to standardized short resting periods (an approximately two-minute resting state) for stable measurement before and after treatment rather than during instrumentation itself. It should be noted that the minimum valid recording length required for EEG α-wave analysis will be maintained for at least two minutes, with no large spikes in waves. All the participants must avoid swallowing saliva, opening or closing the mouth, and body movement during the measurement. In EEG (electroencephalogram) data, sections with noise may show large spikes in delta waves. In EEG data, sections with noise may show large spikes in EEG waves.

This is primarily believed to be caused by significant electromyographic activity, such as body movements or blinking. In MW2, data is output using 4 s windows shifted by 2 s.

This is then averaged over 10 s and exported as a CSV file. Since the numerical values in noisy sections change significantly for only an instant, removing those sections afterward serves as a method to address noise and artifacts. The EEG α-wave activity will be expressed as a mean appearance rate during a predefined resting window. In this feasibility study, the evaluation of EEG α-wave analysis would be a highly exploratory feasible measure.

The baseline value will be established prior to the intervention, and signal analysis will be performed using automated analysis with MemCalc™.

The protocol will be stopped if a significant risk to the research subjects or extreme discomfort is identified. For example, if patients experience adverse events such as epistaxis, discomfort, aspiration/cough events, or desaturation according to vital sign monitoring, the principal investigator should adjudicate the AEs and should stop the protocol.

In this study, safety and infection control in the dental operatory require explicit handling. HFNC therapy introduces airflow, humidification, and interface equipment in a setting with aerosols and cross-infection risk. We will use a single-use circuit and cannula with a built-in filter device. After completion of each session, the AIRVO3 machine will be decontaminated using a special cleaning circuit.

As with conventional hypoxic therapy interventions, there are concerns about the occurrence of adverse events—such as a decrease in SpO_2_—for which a causal relationship cannot be ruled out. According to past reports, the majority of these adverse events are mild to moderate in severity, and studies have shown that they can be rapidly resolved through airway management techniques and control of the depth of sedation. The AIRVO3 device allows for confirmation of SpO_2_ sensor attachment and respiratory rate during monitoring, and an alarm can be set to sound when the SpO_2_ level falls below 90%.

The principal investigator (PI), as the person responsible for evaluation, will ensure that appropriate interventions are implemented for any adverse events of concern. It has been noted that high-flow nasal cannulation may generate aerosols when the flow rate exceeds the patient’s tidal volume, and the use of surgical masks, goggles, and rubber gloves is mandatory during the procedure to prevent operator infection. These measures have been proven effective in preventing aerosol-transmitted infection during the COVID-19 pandemic.

A questionnaire survey will score dental treatment comfort using a 5-point scale across 9 items (1: Not at all, 2: Slightly, 3: Somewhat, 4: Quite a lot, 5: Very much). (File S1)

Q1:Did your body tense up during treatment?Q2:Did your breathing become faster during treatment?Q3:Did you sweat during treatment?Q4:Did you feel nauseous or experience vomiting during treatment?Q5:Did your heartbeat quicken during treatment?Q6:Was it easy to breathe through your nose during treatment?Q7:Were you able to swallow saliva or water residue effectively during treatment?Q8:Did you feel anxious during treatment?Q9:If you were to use it again, which method would you prefer: the first or second?

For Q1~Q8, the Likert scale will be administered in numerical order.

Q9 (Nominal scale: preference) will be administered only after the second session and will be used as a distinct nominal item.

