### 2.6. Outcomes (Table 1)

#### 2.6.1. Primary Feasibility Outcomes

The primary feasibility outcomes are as follows:Recruitment ≥ 5/month (30 cases/6 months);Retention rates ≥ 70%;Patient tolerance and acceptability of the HFNC during dental treatment ≥ 80%;Completeness of physiological and questionnaire-based data collection ≥ 80%;Occurrence of device-related adverse events at less than 5% (less than one case).

**Table 1 dentistry-14-00208-t001:** Outcomes table.

Category	Outcome	Purpose
Primary (Feasibility)	Recruitment, retention	Trial feasibility
	Acceptability, tolerance	Practical implementation
	Data completeness	Outcome feasibility
	Adverse events	Safety
Secondary (Exploratory)	Pulse rate, respiratory rate	Stress physiology
	HRV (LF/HF)	Autonomic response
	EEG alpha activity	Neurophysiological stress
	Questionnaire	Patient-centered outcomes

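### Noisy EEG sections are removed after recording on a qualitative criterion with no stated masking, which could bias the exploratory alpha-wave comparison and decide whether a recording is valid

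*Protocol article*

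**What the plan says.** Section 2.5 (Study Procedures) limits EEG recording to "standardized short resting periods (an approximately two-minute resting state) for stable measurement before and after treatment". It sets a validity condition: "the minimum valid recording length required for EEG α-wave analysis will be maintained for at least two minutes, with no large spikes in waves". On processing, the output of overlapping 4 s windows is condensed: "This is then averaged over 10 s and exported as a CSV file". Noise is then dealt with after the recording: "removing those sections afterward serves as a method to address noise and artifacts". The same section says in general terms that "the missing or low-quality signal segments will be carefully checked with existence of large artifact or noise signals". It gives no amplitude threshold, no limit on how much may be removed, and no statement on whether the person cleaning the file knows the session.

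For ECG the section differs: "automatic processing for arrhythmia detection and noise removal will be applied". It also says that "signal analysis will be performed using automated analysis with MemCalc™".

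Section 2.1 describes an open-label, fixed-sequence study: no HFNC in session 1, HFNC in session 2. Section 2.6.3 plans a mean difference between the two conditions with a 95% confidence interval for continuous outcomes and no hypothesis testing. Section 2.6.1 lists among the primary criteria "Completeness of physiological and questionnaire-based data collection ≥ 80" per cent.

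**The concern.** Deciding that a stretch of EEG is noise is a choice made after the values exist. If it rests on what looks like a large spike, two people can clean the same file differently, and one person can clean two files differently. Here the order of conditions is the same for everyone, so knowing the visit is knowing the treatment.

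Artefact load may also differ between sessions. Section 2.5 names swallowing and body motion as EEG artefact sources, and the Discussion proposes that HFNC changes breathing and swallowing. Borderline sections might then be more frequent in one session, and that is where discretion matters.

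Two things are at stake. The first is the alpha-wave difference between sessions. It is exploratory, but the Limitations section says that the EEG and ECG data will guide outcome selection and sample size for later studies. The second is validity: the planned recording is about as long as the minimum, so there is little or no slack to absorb a removed block.

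**Working it through.** The plan has no figure of its own to reproduce here; no power calculation or EEG variance is given. The checks below size the exposure.

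**Inputs from the article.** Rest period about 120 s, export in 10 s averages, minimum valid length 120 s (all section 2.5); target of 30 participants (section 2.6.4); completeness of at least 80% (section 2.6.1).

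**1. Slack in the recording.**
- Blocks per recording: 120 / 10 = 12.
- Length after removing k blocks: 120 − 10k, which gives 110 s, 100 s and 90 s for k = 1, 2, 3.
- All three are below 120 s. If the minimum applies to what is left after cleaning, one removal makes a two-minute recording invalid. If it applies to the raw recording, it does not. The text does not say which.

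**2. Shift in a session mean if removal is selective.** Assumption: 12 independent, normally distributed blocks, with the k lowest dropped in one session and none in the other. The simulated shift in that session's mean, in units of the within-recording block SD, is:

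| k dropped | shift |
|---|---|
| 1 | 0.15 |
| 2 | 0.28 |
| 3 | 0.39 |

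The same point in alpha percentage points: if the k dropped blocks average d points below the rest, the mean rises by k × d / 12. Both values of d are assumptions, since the article gives none.
- d = 10: 0.8 points for k = 1 and 1.7 for k = 2.
- d = 20: 1.7 points for k = 1 and 3.3 for k = 2.

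These figures show what a one-sided cut can do. They do not estimate the bias in this trial. They also require that a shortened recording still be analysed. If removal is unrelated to session, the expected shift between sessions is 0.

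**3. Sensitivity of the completeness count.** Assumption: each of 30 participants is counted once as complete or not; the article does not define the unit. The mark is 0.80 × 30 = 24. The probability of reaching it is P(X ≥ 24 − b), where X is binomial(30, p) and b is the number of borderline participants leniently counted as complete:

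| true completeness p | b = 0 | b = 1 | b = 2 | b = 3 |
|---|---|---|---|---|
| 0.75 | 0.348 | 0.514 | 0.674 | 0.803 |
| 0.80 | 0.607 | 0.761 | 0.871 | 0.939 |

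This exposure comes from having no objective rule for a valid recording. The count is not a contrast between sessions, so hiding the session would not remove it.

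**The case against.** Several points on the other side are sound.

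- **ECG.** A reader might infer that ECG segments and LF/HF are cleaned by judgement as well. The article does not support that: arrhythmia and noise handling is stated to be automatic, and LF/HF is computed over a fixed 2 min segment. The general sentence on checking low-quality segments does not say that they are removed. The point is confined to EEG.
- **Primary outcome.** A reader might infer that masking would protect the primary completeness criterion. It would not. Completeness covers physiological and questionnaire data together, is not compared between sessions, and is not said to be counted in valid session pairs. Only an objective rule helps there.
- **Who decides.** The article names no reader and does not say that sections are removed by eye. A software rule may exist. What stands is that the published criterion is qualitative.
- **Condensed article.** A full protocol or analysis plan may set the threshold and the masking, so their absence here proves nothing about those documents. But this article goes into processing detail down to window lengths and export format, and the rejection criterion it then gives is loose.
- **Consequence.** Section 2.5 calls the EEG analysis highly exploratory, no testing is planned, and HFNC is fully confounded with period, as the Limitations largely concede. Artefact is also limited in advance by closed eyes, rest-only recording, and no swallowing or movement. All of this stands and keeps the priority low. Period confounding cannot be removed from this design, whereas discretion in cleaning can.

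**Conclusion.** The point holds for EEG. Sections are removed after recording on a qualitative criterion, with no stated cut-off and no stated masking, in a design where the visit reveals the condition. This could bias the exploratory alpha-wave difference. The size is unknown: the one-sided cuts shown above (about 0.15 to 0.39 block SDs) are illustrations under assumed independence and normality. Separately, the rest period and the minimum valid length nearly coincide, so a single 10 s removal can decide validity unless the rule says otherwise.

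The two remedies do different work: masking protects the contrast between sessions, and the numeric rule protects the completeness count. This is a cheap improvement to an exploratory outcome and of low priority. It does not undermine the feasibility aim.

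**What to change.** In section 2.5:

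1. State one numeric EEG rejection rule, the same for both sessions.
2. State when a recording is still valid after removal, and whether the two-minute minimum refers to the raw or the cleaned length.
3. Strip date and session labels from the exported files and give them random codes. Have the existing analyst apply both rules to the coded files.
4. Lock these decisions before the codes are joined to session.
5. Report the share of sections removed in each session.

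The cost is small but not nil: a file-renaming script, a short addition to the text, and a short delay before results by session can be seen. The sample size, the patient procedures and the 80% criterion do not change.

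### Section 2.5 gives extreme discomfort, then plain discomfort, as grounds to stop the protocol, and does not say whether the session, the participant or the study is stopped

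*Protocol article*

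**What the plan says.** All the statements on stopping are in section 2.5 (Study Procedures) of the protocol article.

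- **Rule:** "The protocol will be stopped if a significant risk to the research subjects or extreme discomfort is identified".
- **Example of the rule (the next sentence):** its list of triggers and the response read "epistaxis, discomfort, aspiration/cough events, or desaturation according to vital sign monitoring, the principal investigator should adjudicate the AEs and should stop the protocol".
- **Flow step, earlier in the same section:** HFNC starts at 20 L/min. "If no discomfort is reported, the flow rate will be gradually increased to a maximum of 30 L/min". The article does not spell out what happens when discomfort is reported.
- **Criteria mentioned but not printed:** the device settings refer to "criteria for flow escalation and discontinuation".
- **General response to adverse events:** the principal investigator "will ensure that appropriate interventions are implemented for any adverse events of concern". Stopping is not mentioned there.

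Section 2.6.1 lists the primary feasibility outcomes. Three matter here: "Patient tolerance and acceptability of the HFNC during dental treatment ≥ 80" per cent, "Retention rates ≥ 70" per cent, and a limit on device-related adverse events of under 5%, glossed as fewer than one case. Section 2.6.4 sets the target at 30 participants.

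**The concern.** An example cannot be broader than the rule it illustrates. If the word extreme has force, the example is wrong to list discomfort without it. If any adjudicated discomfort leads to a stop, the qualifier in the rule is empty. Two staff members following adjacent sentences could manage the same patient differently.

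The object of the stop is also open. The rule speaks of research subjects in general, which points towards the study. The example speaks of patients having events, which points towards the individual. Ending an HFNC session, withdrawing a participant and closing the study are different actions with different consequences for the data.

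Both ambiguities bear on participant safety. They can also carry through to two primary outcomes, tolerance and device-related adverse events, because the example itself classes discomfort among adverse events.

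**Working it through.** The plan prints no figure on this point and has no power calculation to reproduce. The check is a comparison of the text, followed by a count against the plan's own thresholds.

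**Step 1: the sentences side by side.**

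| Place in section 2.5 | Condition | Action printed |
|---|---|---|
| Flow step | no discomfort reported | raise flow, up to 30 L/min |
| Stopping rule | significant risk or extreme discomfort | stop the protocol |
| Example of the rule | discomfort, epistaxis, aspiration or cough, desaturation | investigator adjudicates and stops the protocol |

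Rows two and three conflict on severity. Row one is compatible with row two: lesser discomfort need only mean that the flow is not raised. It fits poorly with row three read literally, because a patient reporting any discomfort would be stopped rather than merely not escalated. There are therefore two competing readings.

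**Step 2: the thresholds in patients (n = 30).**

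- Tolerance of at least 80%: 0.80 × 30 = 24 tolerant, so up to 6 not tolerating.
- Retention of at least 70%: 0.70 × 30 = 21, so up to 9 lost.
- Adverse events under 5%: 0.05 × 30 = 1.5, so 1 case (1/30 = 3.3%) is allowed. The gloss of fewer than one case allows 0. The two forms of this criterion do not agree at n = 30.

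**Step 3: can the reading change the verdict?** The documents give no discomfort rate, so the counts below are assumptions. It is also assumed that a stop counts as intolerance and that discomfort leading to a stop counts as a device-related event. Let d be the number reporting any discomfort and e the number with extreme discomfort. Tolerance is (30 − d)/30 or (30 − e)/30; the event rate is d/30 or e/30.

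| d, e | Any discomfort stops: tolerance; events | Extreme discomfort stops: tolerance; events |
|---|---|---|
| 6, 1 | 80.0%; 20.0% | 96.7%; 3.3% |
| 8, 1 | 73.3%; 26.7% | 96.7%; 3.3% |
| 9, 0 | 70.0%; 30.0% | 100%; 0% |

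Each patient moves tolerance by 1/30 = 3.3 percentage points. The tolerance verdict differs between readings when d is 7 or more (23/30 = 76.7%) and e is 6 or fewer. With only 21 patients reaching the HFNC session, the threshold needs 17 tolerant (17/21 = 81.0%), so the verdict can differ from d = 5 (16/21 = 76.2%). In all three rows the adverse-event limit of 5% is met under one reading and missed under the other; with e = 1, the stricter gloss of fewer than one case is missed under both.

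**Step 4: the level of the stop.** A feasibility plan that accepts 6 of 30 patients not tolerating HFNC, and 9 of 30 not retained, expects to continue after individual failures. A study-level stop at the first listed event fits poorly with that.

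**The case against.** The strongest defence is that the second sentence opens as an illustration, so discomfort there should be read as the extreme discomfort just named, with the investigator's adjudication acting as the severity filter. This is a plausible account of what was meant. It does not settle the wording, because the sentence asks the investigator to adjudicate and to stop, and gives no grade to adjudicate against.

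It can also be said that detailed criteria belong in the full protocol and that the article points to them. That stands as far as it goes: the lack of grades or of a separate study-level pause rule is no finding here. Two printed sentences that disagree are a different matter.

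Four stronger readings are tempting, and the documents do not support them.

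- **A reader might infer three incompatible responses to discomfort.** The flow step prints only the no-discomfort branch. Holding the flow is an inference, and it is compatible with stopping for extreme discomfort.
- **A reader might infer that the first cough ends the trial.** With an assumed per-session event rate p, the chance of at least one event in 30 sessions is 1 − (1 − p)^30: 45.5% at 2%, 78.5% at 5%, 95.8% at 10%. The arithmetic is right, but the rates have no source in the documents and the tolerance and retention criteria make the study-level reading unlikely.
- **A reader might infer that data completeness must suffer too.** EEG is recorded at rest before and after treatment and the questionnaire follows treatment, so stopping HFNC need not lose either.
- **A reader might infer that adjudication comes too late to protect the patient.** Nothing says that the investigator is away from the chair.

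**Conclusion.** The point holds as a contradiction in a printed safety rule: adjacent sentences give different severity triggers, and the level at which the protocol stops is undefined. The plain-discomfort reading is also hard to square with the flow step.

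The effect on outcomes is conditional. Section 2.6.1 does not define tolerance as the absence of a stop, and does not say that every discomfort is a device-related event. If stops are counted as intolerance, the illustrative case of 8 reports with 1 extreme puts tolerance at 73.3% or 96.7%, on either side of the 80% threshold. With 6 reports or fewer among 30 patients, tolerance passes under both readings. The size therefore rests on assumed counts; the conflict in the text does not. No view is taken on which clinical rule is right.

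**What to change.** Before enrolment, or by amendment if it has begun, the sponsor should:

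1. reconcile the stopping rule and its example in section 2.5 with each other and with the flow step, so that one statement covers discomfort, epistaxis, cough or aspiration, and desaturation;
2. state whether stopping the protocol applies to the HFNC session, the participant or the study;
3. make the tolerance and adverse-event outcomes in section 2.6.1 count events consistently with the reconciled rule, and align the 5% limit with its gloss.

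The clinical threshold, and who acts on it, are for the sponsor to decide. The cost is protocol wording, with no added patients or visits. The small downside is that some sessions may be classified differently from how they would be under the present text.
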